### Blinding

Due to the particularity of ILM treatment, it is difficult to deceive patients and clinicians during the study. However, the outcome evaluators, data collectors, and analysts will know nothing about the grouping and treatment of patients.

### Interventions

Moxibustion treatment in the two groups (approximately 30 min in duration) will be administered three times per week over six weeks, and a follow-up evaluation will be performed at week 10. During the trial period, the participants will be prohibited from receiving relevant treatments, such as knee surgery, diagnostic arthroscopy, intra-articular injection, physiotherapy, acupuncture, massage therapy, and acupoint application.

Both knees of subjects with bilateral osteoarthritis will be treated, but only the most painful knee will be selected for evaluation in each subject. If both knees are equally painful, the knee with the higher KL grade will be chosen [35], if the knee pain and KL ratings are the same on both sides, the knee joints for evaluation will be randomly selected using a random number table.

### Selection of acupoints

Four acupoints, two obligatory acupoints and two adjunct acupoints will be selected for treatment (Fig. 2). The obligatory acupoints are *dubi* (ST35) and *neixiyan* (EX-LE5), and the adjunct acupoints include *liangqiu* (ST34), *xuehai* (SP10), *yinlingquan* (SP9), *yanglingquan* (GB34), and *zusanli* (ST36). Moxibustion will be applied at two of the five adjunct acupoints according to the location of pain and traditional Chinese medicine (TCM) syndrome differentiation for each person. All acupoints will be located according to the “*WHO Standard Acupuncture Point Locations in the Western Pacific Region*” [36].

**Fig. 2 Fig2:**
[figure not shown]
^Locations of acupoints. The round pink marks represent two obligatory acupoints, and the round blue marks represent five adjunet acupoints^

### Combined medication

The use of hormones and opioids will be prohibited during the trial. Participants who have taken medication for hypertension, diabetes, or knee pain in the month prior to the start of the trial will continue to take medication during the study but will be required to specify the medication in the case report form (reasons, drug name, type, dose, the time of the intake, and whether the symptoms are relieved after taking the medicine). If the participants are not taking any medications before the trial, they will not take any medications during the study. If the patient develops new symptoms or diseases during the trial, any new drug should be approved by the investigator and should only be used if it does not affect the results of trial.

### ILM group

The device used for treatment in the ILM group will be the ILM shown in Fig. 3 (Chongqing Baixiao Medical Equipment Co. Ltd., model type BX-AJY-001).And the parameters of ILM are shown in Table 1.

**Fig. 3 Fig3:**
[figure not shown]
Moxibustion devices. **A** Infrared ceramic graphene moxibustion device. **B** traditional moxibustion device

**Table 1 Tab1:** Infrared laser moxibustion parameter

	Parameter
Device	Infrared ceramic graphene moxibustion instrument (Model: BX-AJY-001)
Rated power	600VA
Power condition	a.c.220 V, 50 Hz
Peak wavelength	3.98 µm
Mode	Continuous

Before treatment, the participant will be in the sitting or supine position, and the acupoints will be cleaned and disinfected with cotton balls soaked with 75% alcohol. The researchers will then fix the moxibustion head on the corresponding part of the skin with Velcro and connect the wires. During treatment, the researchers will first turn on the power, start the corresponding moxibustion head on the intelligent terminal. The infrared radiation source of each infrared moxibustion head used in the test will be 5 cm away from the skin. The diameter of the ILM chamber in contact with the skin is 4 cm. Each treatment will last for 30 min.

The design of ILM is aimed at imitating the actual situation and characteristics of TM burning. When the temperature of heat source is 470 °C, the corresponding temperature of human skin surface can reach about 45 °C, which is consistent with TM [25, 37]. If the participant has no obvious thermal sensation or temperature intolerance, the temperature of the infrared radiation source moxibustion can be gradually increased or decreased to a certain extent on the basis of 470 °C. The moxibustion temperature should be tolerable and comfortable for the participants. During treatment, the patient’s general condition will be observed and recorded.

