### Inclusion criteria

The inclusion criteria were as follows:Diagnosed with KOA according to the American College of Rheumatology criteria [28].Aged 40–70 years old.Average pain score of 4 or more out of 10 on the numeric rating scale (NRS) [29].Average severity score of 48 or less on the Western Ontario and McMaster Universities Osteoarthritis Index (WOMAC) [30].Standard radiographs with Kellgren–Lawrence (KL) grade II or III [31].Written informed consent.With basic reading and comprehension skills.

Participants who fulfill the above seven criteria can be included in the trial.

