### Exclusion criteria

The exclusion criteria were as follows:Received knee surgery in the past six months or waiting for surgery.Received acupuncture treatment for KOA in the past three months.Received an intra-articular injection for KOA in the past six months.Received arthroscopy for KOA in the past year.Had other diseases, infections, or traumatic injuries that could cause knee pain.Had serious cardiovascular and cerebrovascular, respiratory, liver, kidney, metabolic system and other diseases, malignant tumors, mental disorders.Allergic to moxibustion smoke or infrared light.Pregnant or lactating.Received other similar physiotherapy methods in the past month.

Participants who met at least one of the exclusion criteria above will be excluded from the trial.

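### The ILM heat may be raised because a participant feels little warmth, yet no printed eligibility criterion screens for reduced heat sensation at the knee

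*Protocol article*

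**What the plan says.** **Heat rule.** The ILM group section of the protocol article gives a starting source temperature of 470 °C, at which "the corresponding temperature of human skin surface can reach about 45" °C, for 30 minutes per session. It then states: "If the participant has no obvious thermal sensation or temperature intolerance, the temperature of the infrared radiation source moxibustion can be gradually increased or decreased". The size of the change is described only as "gradually increased or decreased to a certain extent on the basis of 470" °C. Two further sentences bear on it: "The moxibustion temperature should be tolerable and comfortable for the participants", and the patient's "general condition will be observed and recorded" during treatment.

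**Who may enter.** The Inclusion criteria section lists seven items and closes with "Participants who fulfill the above seven criteria can be included in the trial". The Exclusion criteria section lists nine items and closes with "Participants who met at least one of the exclusion criteria above will be excluded from the trial". The broadest exclusion reads: "Had serious cardiovascular and cerebrovascular, respiratory, liver, kidney, metabolic system and other diseases, malignant tumors, mental disorders".

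**Related text.** The Combined medication section lets participants already treated for diabetes continue their medication. The Safety assessment section includes scalds and blisters among the most common treatment-related adverse events. The Study quality control section describes training of treating staff in the operation of both devices, and a specialist supervisor at each site.

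**The concern.** A dose rule led by sensation works when the participant can feel and report heat. It works in the wrong direction when the participant cannot. For someone with reduced heat sensation, the trigger for more heat is present and the signal to stop is weakened. If such a person can pass the entry criteria, following the text as written could give more heat to the participant least able to warn of a burn.

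What is at stake is avoidable skin injury in the ILM arm. The article already foresees this kind of harm, and it presents ILM as a possible safer alternative to traditional moxibustion. No statistical quantity is at stake.

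**Working it through.** No power or error-rate formula applies. The check is a count of the criteria and a reading of the heat rule beside them.

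**1. Direction of the rule.** The sentence pairs two conditions with two actions. In order, no obvious sensation goes with an increase and intolerance goes with a decrease. The opposite pairing would raise heat for someone who cannot tolerate it, so the first reading is the only sensible one.

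**2. Limits on an increase, as printed (ILM group section).**

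| Limit | Does it hold if sensation is reduced? |
|---|---|
| Change is gradual | Slows the rise but does not cap it |
| Change is of limited but unstated extent | No source or skin temperature is given |
| Heat must be bearable and comfortable | Relies on the same sensation |
| General condition observed | No check of the skin is stated |

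**3. Count of the criteria.**
- Inclusion: diagnosis, age, pain score, WOMAC score, radiographic grade, consent, reading ability = 7. This matches the article's own count of seven.
- Exclusion: knee surgery, acupuncture, intra-articular injection, arthroscopy, other causes of knee pain, serious systemic disease, allergy to smoke or infrared light, pregnancy or lactation, similar physiotherapy = 9. The article gives no total here.
- Total: 7 + 9 = 16. Number naming heat sensation, sensory loss or neuropathy: 0 of 16.

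**4. Nearest exclusions.** Allergy to smoke or infrared light is a different risk. The serious-disease item turns on seriousness and does not mention sensation. An investigator might apply it to some cases, but the text does not direct this.

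**5. Exposure.** Interventions section: 3 sessions per week × 6 weeks = 18 sessions at which the rule is available to one ILM participant. The planned ILM arm is 37, fewer if some decline ILM under the Zelen procedure. The documents give no figure for how many have reduced heat sensation, and none is assumed.

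**6. Timing.** The Trial status section says that recruitment is under way and expected to finish by November 2023. The article is dated 2 December 2023. A change that acts only at enrolment may therefore reach few people, whereas a change to the heat rule reaches anyone still under treatment.

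**The case against.** The strongest reply is that this is a condensed article and that the operating procedures and device manual are not shown. Treating staff are trained in the device and in managing adverse events, and a specialist supervises each site. A temperature ceiling or a skin check may well be in those materials. That stands for the printed limits on heat: they describe the article and not necessarily practice. It is weaker for eligibility, because the article prints both lists and says that they decide entry.

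The wording is also milder than a quick reading suggests. It speaks of no *obvious* sensation and permits, without requiring, a gradual change. A reader might infer that staff must keep heating a participant who feels nothing. The text does not say that.

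A reader might also infer from the diabetes medication clause that participants with nerve damage are expected. The documents do not mention neuropathy. The clause shows only that treated diabetes is not in itself a bar to entry.

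Traditional moxibustion also leans on sensation: its heat is adjustable, and fading warmth is one sign that the column has burned out. But only the ILM text ties an increase to absent sensation.

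Finally, scalds and blisters are listed without rates and without any link to the adjustment rule, so no size of harm can be derived from the documents.

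**Conclusion.** The point holds as a gap between two printed provisions: heat may be raised for lack of sensation, and none of the 16 printed criteria screens for reduced sensation. A participant with reduced sensation at the knee could be enrolled and given more heat at any of up to 18 sessions.

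This rests on the printed lists being the full entry criteria and on no unseen procedure closing the gap. The number at risk is unknown. The documents do not support a claim that burns are likely, that the device lacks a ceiling, or that the trial's conclusions are affected. The primary endpoint, the margin of −2, the analysis and the target of 74 are unchanged. It is a cheap improvement in patient safety.

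**What to change.** **(a) Exclusion criteria.** Add: *Reduced or absent heat sensation over any knee to be treated.* Existing staff check this at the enrolment assessment, before the envelope is drawn, by asking whether the candidate can tell a warm object from a cool one on the skin there. Checking before allocation applies the criterion equally to both arms. The wording covers any knee to be treated because both knees are treated in bilateral disease.

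**(b) ILM group section.** Amend the heat rule: *The source is not raised above 470 °C for absent sensation unless the participant has shown that they can tell warm from cool at the treatment site. Staff look at the skin before any increase.* This protects participants already enrolled, whom (a) cannot reach. The skin check also helps where a simple warm/cool test misses a milder loss.

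Both changes need Ethics Committee approval, as the Study quality control section requires for any protocol change, and apply from approval onward. The cost is a few candidates not enrolled and a few seconds of checking.

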### TM group

The control participants group will receive TM using the Baixiao moxibustion device shown in Fig. 3 (Dimension: 6.4 cm × 3.8 cm, Chongqing Baixiao Medical Equipment Co. Ltd., model type BX-A002).

The researchers involved in the treatment will paste the moxibustion tube onto the acupoints with positioning paper, remove the moxibustion cover, install the moxibustion column, and buckle the column on the moxibustion tube after lighting. The size of the inlet hole of the moxibustion tube can be adjusted by rotating the tube body left and right or pull and push the tube body up and down to moderate the moxibustion temperature. The diameter of the TM chamber in contact with the skin is 3.8 cm. The distance between the heat source and the skin is adjustable, ranging from 1.5 to 4 cm. Each moxibustion column can burn for approximately 30 min. The burning of the moxibustion column is indicated by the disappearance of the thermal sensation and the cooling of the wall of the moxibustion device.

### Outcomes

The assessment schedule is presented in Table 1.

#### Primary outcome

The primary outcome, to be assessed at the end of the last treatment at week 6, is the change in pain from baseline using the NRS index [38]. The NRS index typically uses a 0–10 range instead of words to represent the degree of pain experienced by the subject: 0 indicates no pain; 1–3 indicates mild pain (occasional pain that generally does not interfere with walking); 4–6 indicates moderate pain (frequent pain that interferes with walking); 7–9 indicates severe pain (sustained pain that seriously interferes with or prevents walking); and 10 indicates the worst/overwhelming pain. At the time of the evaluation, participants will be asked to mark the number on the scale that best represents their pain level in the last 24 h.

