#### Secondary outcomes

The NRS pain score will also be measured at the end of the last treatment each week (weeks 1, 2, 3, 4, and 5). Other secondary outcomes will include the changes in WOMAC, SF-36, knee circumference, and 6-min walking test (6MWT) from baseline to endpoints (weeks 6 and 10):WOMAC: This scale evaluates the comprehensive condition of the knee joint from three aspects: knee pain, stiffness, and daily functional activities. The WOMAC scale contains 24 items, with four points for each item. A higher score signifies worse knee function. The Chinese version of this scale has good reliability and validity [39].SF-36: This scale consists of 36 items, including eight fields of physical function, arole physical, physical pain, general health status, vitality, social function, arole emotional, and mental health, and is used to assess the health-related quality of life of the subject. A higher score indicates better health-related quality of life [40, 41].Knee circumference: The degree of swelling in the subject’s knee was assessed by measuring the knee circumference (i.e., the leg circumference at the center of the upper and lower edges of the patella) in millimeters. A uniform tape measure will be used to measure different patients [42].6MWT: Before the test, researchers will draw a 30-m straight line on flat ground and mark both ends of the line. During the test, the participants will walk back and forth in a straight line at their own speed. The researchers will give the correct time every two minutes and calculate the distance walked by the participant at the end of six minutes. Potential discomfort such as fatigue, dizziness, angina pectoris, dyspnea and cold sweat will be recorded during the trial. The trial will be suspended or discontinued if the patient cannot complete it. During the test, participants will be monitored with a unified wristwatch for basic indicators such as heart rate and blood oxygen. The Borg score of dyspnea and fatigue and other data will be recorded before and after the test (Table 2) [43].

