### Statistical analysis

Statistical analysis will be undertaken using both intention-to-treat (ITT) and per-protocol (PP) analyses. For the ITT analysis, all patients who undergo the Zelen-type randomization and received at least one treatment will be analyzed. Primary PP data analysis will also be undertaken for all patients who have high compliance (patient compliance rates equal to or greater than 80%) and do not use drugs or treatments prohibited by the protocol during treatment.

The statistical analysis will take the form of a non-inferiority test. The margin of non-inferiority is -2. For the main outcome, we will calculate the 95% confidence interval for the difference in NRS pain score between the treatment group and the control group. If the lower limit is greater than -2, non-inferiority will be considered valid.

For continuous data, mean ± standard deviation will be used to describe data that conforms to a normal distribution, whereas non-normally distributed continuous data will be described as the median (interquartile spacing). Where the data conforms to a normal distribution, independent sample t-test will be used for comparison between the two groups with homogeneity of variance; otherwise, a t-test will be used with heterogeneity of variance. Wilcoxon rank-sum test will be used if data does not conform to a normal distribution. Categorical data will be represented by frequency or percentage and compared using chi-square test or Fisher exact test. Missing data will be replaced according to the last observation carried forward method. The 95% confidence interval will be calculated, and *P* < 0.05 will be considered to indicate a significant difference. All statistical analysis will be performed using SPSS software (version 20.0).

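### The primary pain score is tied to a week-6 treatment session, so participants who stop treatment but stay in the trial have no observed week-6 score and enter the ITT analysis with an older one

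*Protocol article*

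**What the plan says.** The Primary outcome section sets the timing: "The primary outcome, to be assessed at the end of the last treatment at week 6, is the change in pain from baseline". The Abstract ties the primary outcome to the same point. Under Secondary outcomes, the ratings for weeks 1 to 5 follow the same pattern: "The NRS pain score will also be measured at the end of the last treatment each week".

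The other efficacy measures (WOMAC, SF-36, knee circumference and the 6-minute walk) are placed at weeks 6 and 10 without reference to a session. The NRS is not among the outcomes listed for week 10.

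On treatment, the Interventions section states that sessions "will be administered three times per week over six weeks, and a follow-up evaluation will be performed at week 10".

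Under Statistical analysis, the ITT rule is that "all patients who undergo the Zelen-type randomization and received at least one treatment will be analyzed". The per-protocol set requires "patient compliance rates equal to or greater than 80" per cent and no prohibited drug or treatment. How compliance is counted is not stated. Missing data are to be filled by last observation carried forward (LOCF).

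**The concern.** An ITT analysis needs the outcome from people who stop treatment as well as from those who continue. Here the text makes the primary rating depend on attending a session. Someone who stops treatment and remains willing to be followed has no stated occasion for the week-6 rating, although the same text puts the other week-6 measures at a time point that does not depend on a session.

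Stopping need not be unrelated to treatment. It could follow from poor relief, for example, or from the skin reactions that the Safety assessment section lists as the most common treatment-related events. Missing week-6 scores would then be linked to treatment experience, and LOCF would replace them with scores from a different time. In a non-inferiority comparison this matters because carrying early scores forward in both arms can shrink a real difference towards zero, which favours the non-inferiority conclusion.

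**Working it through.** **1. Where the NRS can be observed, reading the text literally**

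| Measure | Stated time | Depends on attending a session? |
|---|---|---|
| NRS, weeks 1–5 | end of each week's last session | yes |
| NRS, week 6 (primary) | end of the last session at week 6 | yes |
| WOMAC, SF-36, knee circumference, 6MWT | weeks 6 and 10 | not stated to |
| NRS, week 10 | not listed | – |

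So a participant without a week-6 session has no observed week-6 NRS. LOCF supplies the latest weekly score. If the participant stopped before the first weekly rating, the only score to carry is baseline, and the change is 0.

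**2. Who can reach the per-protocol set this way**

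Inputs: three sessions a week for six weeks (Interventions); threshold 80% (Statistical analysis). Assumption: compliance = sessions attended ÷ sessions planned.

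- Planned sessions: 3 × 6 = 18.
- Threshold: 0.80 × 18 = 14.4, so at least 15 sessions.
- Weeks 1–5 complete, week 6 absent: 15/18 = 83.3%, admitted.
- One further session missed: 14/18 = 77.8%, excluded.
- Stopped after week 4: at most 12/18 = 66.7%, excluded.

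Exactly one attendance pattern is admitted without a week-6 session, and LOCF then uses the week-5 score.

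**3. How many participants**

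The only related figure is the maximum dropout of 25% (Sample size calculation): 0.25 × 37 = 9.25 per arm, or 0.25 × 74 = 18.5 in all. This mixes people who leave the trial altogether, people who might leave between weeks 6 and 10 after giving the primary rating, and people who stop treatment but stay. Only the last group is affected by the timing rule, and the documents give no number for it.

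**4. What carried-forward scores could do (illustration only)**

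Assume that a fraction *p* in each arm carries baseline forward, and that the true difference in mean change is 2 points, the size of the margin. The analysed difference is 2 × (1 − *p*):

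- *p* = 5%: 1.9
- *p* = 10%: 1.8
- *p* = 25%: 1.5

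The 25% line is an extreme case, with every permitted dropout treated as a baseline carry-forward. Scores carried from later weeks would dilute the difference less.

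**The case against.** The strongest objection is that the assessment schedule (Table 2) is not shown. Week 6 is also the time point for the other outcomes, so an NRS may be planned there for everyone, and the sentence on the last treatment may only be naming the end-of-treatment time point. A condensed article also commonly leaves visit windows and follow-up after discontinuation to the full protocol. Part of this stands: a calendar-based NRS cannot be ruled out. But the article is not silent on timing. It states a rule for the primary rating, repeats it in the Abstract, uses the same form for the weekly ratings, and words the other measures differently. If Table 2 says otherwise, the text needs to be brought into line with it.

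Stronger readings are tempting, and the documents do not support them:

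- **That these participants have no primary outcome.** LOCF gives them an imputed one. What they lack is an observed week-6 score.
- **That the 80% rule generally admits people who stop early.** Only the single pattern above qualifies, and only if compliance means sessions attended. Someone who misses just the final session may still be rated at the last session attended that week; the wording leaves this open.
- **That about 9 per arm lose their week-6 score because of the schedule.** The 25% is a maximum for all dropout, and those who leave altogether would be missing under any schedule. For the same reason, no gain in precision can be calculated from it.
- **That LOCF must favour non-inferiority here.** The direction depends on which arm loses participants and when. The illustration assumes equal fractions in both arms.
- **That the per-protocol set should require an observed week-6 NRS.** This would select participants on whether their outcome is available, which is debatable, and it does not follow from the timing problem.

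**Conclusion.** The concern holds in limited form. As worded, the primary and weekly NRS ratings depend on attending a treatment session, so participants who stop or miss week 6 but stay in the trial have no observed week-6 NRS and enter the ITT analysis with an older score. The per-protocol set is exposed only for full attendance in weeks 1–5 with none in week 6 (83.3%), on the assumption that compliance counts sessions.

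The number affected cannot be derived. If treatment stoppers are counted among the dropouts, about 9 per arm is a ceiling and the true figure may be much smaller. The conclusion rests on the text alone, because Table 2 is not shown. The change is worth making because ratings that were never collected cannot be recovered at analysis, and collecting them is cheap.

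**What to change.** In the Primary outcome and Secondary outcomes sections, define the NRS at the end of study week 6, and of each of weeks 1 to 5, by a calendar window counted from the first session. State that it is sought from every randomised participant still in the trial, whether or not they attend or continue treatment, and that the blinded evaluator collects it, by phone if there is no visit. Align the Abstract and Table 2 with this wording; if Table 2 already sets a calendar-based rating, only the text needs to change.

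The cost is a wording change, which under the protocol's own rule needs Ethics Committee approval, and a few short calls. The small downside is that some ratings would be given by phone instead of being marked on the paper scale.
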